### Safety

Study participants are monitored weekly during the study intervention for the occurrence of adverse events defined as any undesirable experience. All adverse events are recorded on an adverse event case report form during study interventions and evaluated for relevance to the intervention and severity according to institutional review board mandated criteria by the study rheumatologist. These are reported by category and are examined for trends that could indicate safety risk to the participants with particular emphasis on serious adverse events and any adverse events deemed related to the intervention. This plan has been approved by the Ethics Review Board and the Data Safety Monitoring Board (DSMB). All adverse events are reported to the Human Research Committee promptly in accordance with guidelines.

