## Methods/design

### Study design overview

This study is a single-center, 52-week, randomized controlled trial. Patients with fibromyalgia are randomized to one of four Tai Chi intervention groups: 12 or 24 weeks of supervised Tai Chi held once or twice per week, or a supervised aerobic exercise control twice per week for 24 weeks. All groups will have a 52-week follow-up. The primary outcome is the change in Revised Fibromyalgia Impact Questionnaire (FIQR) total score from baseline to 24 weeks [35].

Outcome measurements are collected at baseline, every week during the intervention period (FIQR and adverse events only), upon completion of the 12 or 24 week program, and at 52 weeks. The staff conducting the physical function assessments and the statistician are blinded to treatment assignment. The specific endpoints and their conceptualization as outcomes or intermediaries are presented in Table 1.

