**Secondary outcome variables**					
Widespread Pain Index	x		x	x	x
Symptom Severity Scale	x		x	x	x
Participant Global Assessment	x		x	x	x
Pittsburgh Sleep Quality Index	x		x	x	x
Patients’ Global fibromyalgia Severity	x		x	x	x
SF-36	x		x	x	x
Beck II Depression Inventory	x		x	x	x
Perceived Stress Scale	x		x	x	x
Chronic Pain Self-Efficacy	x		x	x	x
Social Support Survey	x		x	x	x
Coping Strategies Questionnaire	x		x	x	x
MOS Social Support Survey	x		x	x	x
OES for exercise	x		x	x	x
OES for Tai Chi/AE		x			
PROMIS^b^	x		x	x	x
Health Assessment Questionnaire	x		x	x	x
NEO Five-Factor Inventory^c^	x		x	x	x
Five Facet Mindfulness	x		x	x	x
Credibility-Expectancy^d^	x			x	x
Pre-clinical disability	x		x	x	x
The Hospital Anxiety and Depression Scale	x		x	x	x
CHAMPS activities	x		x	x	x
Functional Performance Tests^e^	x		x	x	x
Body mass index	x		x	x	x
Medications	x		x	x	x
Adverse events	x	x			
Adherence	x	x	x	x	x

^a^Revised Fibromyalgia Impact Questionnaire (FIQR) is the primary outcome at 24 weeks; the other collection times are secondary outcome variables. ^b^Participant-Reported Outcomes Measurement Information System (PROMIS) questionnaires include PROMIS Pain Impact, PROMIS Physical Function, PROMIS Depression, PROMIS Anxiety, PROMIS Sleep Disturbance, Satisfaction with Social Roles, and PROMIS Health Assessment Questionnaire. ^c^The NEO Five-Factor Inventory is given out once over the course of the study at the earliest available evaluation period. ^d^The Credibility-Expectancy Questionnaire is given out before the start of the first intervention session. ^e^Functional Performance Tests include timed chair stand, one leg stand, 6-minute walk, and muscle strength and power. AE, aerobic exercise; MOS, Medical Outcome Study; OES, Outcome Expectations Scale; SF-36, Medical Outcome Survey Short-Form 36; CHAMPS, Community Health Activities Model Program for Seniors

The study setting is an urban tertiary care academic hospital, Tufts Medical Center, in Boston, Massachusetts, USA. The study received ethics approval from the Tufts Medical Center/Tufts University Institutional Review Board (approval number 9945).

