### Tai Chi intervention

The participants randomized to Tai Chi will practice at Tufts Medical Center. A detailed description of a standardized Tai Chi protocol was prepared and tested in our previous trials [23,25,26,32,39]. The three Tai Chi instructors each have extensive experience (>20 years) conducting Tai Chi mind-body programs and follow a Tai Chi protocol specifically designed for individuals with chronic pain. In addition, all three instructors completed the required research and human subject protection training prior to initiation of the intervention classes.

To ensure that instructors are prepared to teach a robust, standardized Yang-style Tai Chi treatment program for patients with fibromyalgia, we conduct a training session with the three Tai Chi instructors to thoroughly review concepts of fibromyalgia and a standardized teaching protocol at the beginning of the study and are doing reviews as needed throughout the course of the study. All sessions are monitored by regularly reviewing video recordings and providing feedback throughout the study to ensure proper instruction.

Each Tai Chi session lasts 60 minutes and continues once or twice a week for 12 weeks or 24 weeks. Participants are also provided with printed materials on the Tai Chi Mind-Body program, including Tai Chi principles, practicing techniques, and safety precautions for participants with fibromyalgia. In the first session, the Tai Chi instructor explains exercise theory and Tai Chi procedures. For the remaining sessions, the procedures include the following components: (1) warm-up and a review of Tai Chi principles and techniques; (2) Tai Chi movement; (3) breathing techniques; and (4) various relaxation methods. All program components are derived from classical Yang style Tai Chi 108 postures [42]. Due to time limitations [22] we condensed the 108 postures of Classical Yang style Tai Chi to 10 forms that could be learned by participants with a chronic pain condition within 12 or 24 weeks. The 10 forms were selected because: (1) they are easily comprehensible; (2) clearly represent progressive degrees of stress to postural stability, with weight bearing moving from bilateral to unilateral supports; and (3) seem to emphasize increasing magnitude of trunk and arm rotation with diminishing base of support and, as such, will potentially improve physical function without excessively stressing the joints. An outline of the Tai Chi exercise program is shown in Additional file 2.

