
All participants are encouraged to maintain their usual physical activities but to perform no new additional strength training other than their Tai Chi exercises. Participants are also instructed to practice Tai Chi for at least 30 minutes per day at home. Tai Chi instructors remind participants in class to practice daily according to weekly assignments of Tai Chi poses. The data collected for class attendance are recorded and verified using standard case report forms that include a participant sign-in sheet as well as a staff-completed attendance sheet to confirm accurate attendance recordings.

After completing the 12 or 24 week treatment sessions, participants are asked to continue with their exercises. The research team monitors these participants once a month with home calls until the 52-week follow-up evaluations. All participants are asked to record their exercise behavior until the end of 52 weeks. This is the same for the aerobic exercise group, described below.

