### Aerobic exercise training

Participants randomized to aerobic exercise receive a closely supervised, group-format cardiovascular (aerobic) exercise program located on our Tufts Campus. The program is consistent with the current recommended guidelines of moderate intensity exercises for fibromyalgia [8,9,21].

In the fibromyalgia population, lower levels of cardiovascular fitness and lower thresholds for post-exercise muscle pain and fatigue are reported [2,3]. Compliance may be compromised due to training that is too intense or to a lack of supervision. Therefore, our program is individually tailored to each participant, closely supervised, introduced in a progressive manner, and gradually increased in volume and intensity to achieve the target of moderate-intensity exercise. The senior scientist in exercise physiology ([name]) has over 20 years experience in conducting exercise trials, oversees the program and runs training sessions for the exercise instructors at study initiation and throughout the trial. The experienced instructors perform the exercise regimen. Each session lasts 60 minutes, twice a week, for 24 weeks. We instruct participants to walk daily on their own, gradually increasing their time until they reach 30 minutes a day. We also provide the participants with printed materials on fibromyalgia and the aerobic exercise program, including aerobic exercise principles, practicing techniques, and safety precautions for participants with fibromyalgia.

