### Sample size

We propose to enroll 216 participants, 144 in the Tai Chi group and 72 in the aerobic exercise group. Power analyses are based on hypothesized changes in FIQR total scores. We used the outcomes of two previous randomized trials to formulate expected effects. Both studies used education controls. The first study by Rooks and colleagues [73] compared the effects of a 16-week aerobic and flexibility exercise program with an education group among 101 participants with fibromyalgia. They found that the aerobic and flexibility exercise group had a 7.9-point mean improvement in the Fibromyalgia Impact Questionnaire (FIQ), yielding an effect size of 0.62. The second study, our pilot trial of 66 participants with fibromyalgia, compared 12-weeks of Tai Chi with a wellness education control [40]. We found an 18.4-point mean improvement in the FIQ score in the Tai Chi group, yielding an effect size of 1.04. We hypothesize that patients receiving Tai Chi will improve more than those receiving aerobic exercise. Using a two-sided hypothesis test at a 0.05 significance level with an allocation ratio of 2:1, a total sample size of 216 (144 in the Tai Chi group, 72 in the aerobic exercise group) would give about 80% power to detect a conservative effect size of 0.4.

We also seek to elucidate how four different schedules of dose and frequency might modify the impact of Tai Chi. With 36 individuals per group, we would have 80% power to detect an effect size of 0.67 between two of these groups with a two-sided 0.05 level test. We will also gain power from the additional individuals tested in the other groups as well as from the blocking by instructor.

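### Routine adverse event recording follows class length, so the two 12-week Tai Chi arms are observed for 12 weeks against 24 weeks in the other arms

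*Protocol article*

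**What the plan says.** Three places in the protocol article set when adverse events are routinely collected, and they agree that it is the intervention period.

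- Safety: "Study participants are monitored weekly during the study intervention for the occurrence of adverse events", and "All adverse events are recorded on an adverse event case report form during study interventions".
- Study design overview: the data collected "every week during the intervention period (FIQR and adverse events only" are those two items, with other measurements at fixed visits.
- Table 1: the row reads "Adverse events x x". The marks fall under Baseline and Intervention, with none at weeks 12, 24 or 52. The Medications row, by contrast, is marked at all three.

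The length of the intervention differs by arm. For Tai Chi: "Each Tai Chi session lasts 60 minutes and continues once or twice a week for 12 weeks or 24 weeks". For aerobic exercise: "Each session lasts 60 minutes, twice a week, for 24 weeks". Table 1, however, labels the Intervention column as months 1-3.

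After classes end, participants in all arms are asked to carry on exercising. On contact in that phase, the Tai Chi intervention section says: "The research team monitors these participants once a month with home calls until the 52-week follow-up evaluations". The aerobic section says the same for its arm. The Adherence section describes these calls as asking about the frequency, duration and type of exercise.

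**The concern.** When the observation window depends on the arm, a raw count or percentage of participants with an event mixes the event rate with the time spent looking. The arms with the short window are all Tai Chi arms, and the trial's leading hypothesis is that Tai Chi is better than aerobic exercise, so a crude table would err in the direction the investigators expect. The same distortion enters the duration question within Tai Chi: 12 weeks of classes would appear safer than 24 weeks simply because recording stopped sooner.

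This is a collection rule, not a detail that an analysis plan could settle later. No analysis can recover events that nobody asked about. The follow-up phase, in which participants practise without supervision, is also the setting closest to the real-world use the article has in mind, and no routine adverse event questioning is described for it.

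**Working it through.** **The plan's own figures.** The article gives no safety figure to reproduce. Its sample size statement is "We propose to enroll 216 participants, 144 in the Tai Chi group and 72 in the aerobic exercise group"; the stated efficacy power of about 80% at effect size 0.4 reproduces (0.791), but nothing below depends on it. Only the arm sizes are used: 144 / 4 = 36 per Tai Chi arm, so 72 in the two 12-week arms and 72 in the two 24-week arms.

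**Observation time, taking the text at its word.**

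- 12-week Tai Chi arms: 72 × 12 = 864 person-weeks
- 24-week Tai Chi arms: 72 × 24 = 1,728
- Aerobic exercise: 72 × 24 = 1,728
- Pooled Tai Chi: 864 + 1,728 = 2,592, and 2,592 / 144 = 18 weeks per person

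The ratio of time per person to the aerobic arm is 12/24 = 0.50 for the 12-week arms and 18/24 = 0.75 for Tai Chi pooled. With a constant and equal rate, these are also the ratios of events per person.

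**Share of participants with at least one recorded event.** The article gives no event rate, so I assume the same constant weekly rate r in every arm, from 0.005 to 0.05. The share after w weeks is 1 − exp(−r × w); pooled Tai Chi is the mean of the 12-week and 24-week shares.

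| Weekly rate | Aerobic (24 weeks) | 12-week Tai Chi arms | Tai Chi pooled | Ratio, 12-week arms | Ratio, pooled |
|---|---|---|---|---|---|
| 0.005 | 11.3% | 5.8% | 8.6% | 0.515 | 0.757 |
| 0.01 | 21.3% | 11.3% | 16.3% | 0.530 | 0.765 |
| 0.02 | 38.1% | 21.3% | 29.7% | 0.560 | 0.780 |
| 0.05 | 69.9% | 45.1% | 57.5% | 0.646 | 0.823 |

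Every ratio would be 1.00 under a common window.

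**Does a rate per person-week solve it?** Only if the rate is constant. Suppose the rate in weeks 13 to 24 is half that in weeks 1 to 12. In units of the early rate, the aerobic average is (12 + 6) / 24 = 0.75, the 12-week arms' is 1.00 and pooled Tai Chi is (12 + 18) / 36 = 0.833. The rate ratios are 1.00 / 0.75 = 1.33 and 0.833 / 0.75 = 1.11, now against Tai Chi. Restricting all arms to weeks 1 to 12 avoids this.

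**Coverage of follow-up.** Planned calendar time is 216 × 52 = 11,232 person-weeks. Routine recording covers 2,592 + 1,728 = 4,320, or 38.5%. If the months 1-3 label were applied literally to every arm, it would be about 216 × 12 = 2,592, or 23.1%. These are alternative readings and do not add up.

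**The case against.** The strongest reply is that the biased comparison is not in the document. The Safety section describes reporting by category and looking for signals of risk to participants, which is monitoring. Neither the hypotheses nor the Data analysis section contains a between-arm adverse event test or summary measure, and the choice of measure may sit in an analysis plan that is not shown. This stands. A reader might infer that the safety comparison favours Tai Chi by design; the article does not support that, because the distortion arises only if crude frequencies are used, and person-week rates could tilt the other way.

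A reader might also infer that nothing at all is captured after classes end. That is too strong. Reporting of serious events and deaths to the Data Safety Monitoring Board carries no stated time limit, the Adherence section mentions staff monitoring of adverse events without an end date, and the questionnaires used on the monthly calls are not reproduced. However, serious event reporting depends on staff coming to know of the event, and the open-ended remark does not override three places that name the intervention period. What remains is that no routine solicitation is stated for follow-up.

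Two further points are fair. Read literally, the months 1-3 label would give every arm the same window and remove the imbalance, though it would leave weeks 13 to 24 of supervised exercise unrecorded in three arms. And the two 24-week Tai Chi arms already share the aerobic arm's window, so an equal-window comparison exists within the design. Finally, the article says the ethics board and the monitoring board approved the safety plan. That shows it was acceptable for protecting participants; it does not make arm frequencies comparable.

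**Conclusion.** The point holds in a limited form. Routine recording of adverse events ends with the intervention, which gives the 12-week Tai Chi arms half the observation time of the aerobic arm and Tai Chi as a whole three quarters of it. At equal true rates, crude percentages would show pooled risk ratios of 0.757 to 0.823, and 0.515 to 0.646 for the 12-week arms. These rest on an assumed constant weekly rate of 0.5% to 5%, equal in all arms, on full retention, and on the text rather than the Table 1 label setting the window.

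Two stronger statements should be avoided. It is tempting to say that Tai Chi is watched for half as long, but that is true of only 72 of 144 participants. It is also tempting to say that most of the exercise exposure goes unobserved; 38.5% is a share of calendar time, and the article gives no figure for how much participants exercise after classes end.

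This should be corrected. It does not touch the primary efficacy result, but it determines whether a safety statement about Tai Chi against aerobic exercise, or about 12 against 24 weeks of Tai Chi, can be trusted.

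**What to change.** 1. Ask about adverse events in all arms at the existing monthly calls and at the week 12, 24 and 52 visits. Show these events separately from weekly in-class capture, because recall by telephone or at a visit is less complete.
2. Make weeks 1 to 12 the main window for comparing arms. Add the two 24-week Tai Chi arms against aerobic exercise over weeks 1 to 24.
3. Give rates per person-week only as a supplement, stating that they assume a constant rate.
4. Reconcile the months 1-3 label of the Intervention column in Table 1 with the 24-week interventions in the text, so that one recording window is stated.

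The cost is one item on contacts that already take place, a correction to a table label and a few lines of analysis wording. For participants who have already finished, items 2 and 3 need no new data, provided recording followed the text. If item 1 starts partway through the six cycles, call-based events should be compared within cycle, since the aerobic arm runs in every cycle and each Tai Chi schedule in only three.

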### Plan for monitoring depression

We are using the BDI-II to screen, monitor, and analyze depression The BDI is administered throughout the study to monitor depressive symptoms in participants (once a month during intervention, and then at each follow-up visit). If an enrolled participant obtains a BDI score >28, marking severe symptom severity during the study, the study physician and primary investigator will advise the individual to seek medical help outside of the study. The intake telephone number to the Tufts Medical Center outpatient psychiatry department is provided if the individual requests a referral. It is important to note that the BDI is being used to monitor depressive symptoms which may influence compliance and outcome of this study based on our extensive experience from prior trials [35].

### Data management

In accordance with our study protocol, we have extensive procedures in place to ensure quality control of data collection, data entry, and subject confidentiality. Study data are to be collected and managed using the REDCap electronic data capture system [72]. Participants who are not able to directly enter data into the REDcap system will be asked to fill out paper case report forms, which are entered into REDCap by study staff. These case report forms will then be filed in the participants’ file and stored in the principal investigator or study coordinator’s office in locked filing cabinets. No participant identifiers are included in the study database. Data are exported from the database into statistical software for analysis. Additionally, REDCap has an audit trail that records every time a participant or staff member makes changes to any data entered on the website. All case report forms are either collected in a REDCap Database, a secure online database, or on paper record, which are kept in a secure and lock-protected location. The primary outcome, the FIQR, is measured by an initial staff member then re-measured by a second staff member. In addition, the measurement is entered into the REDCap Database by an initial staff member then the data entry is double checked by a second staff member. The statistician ([name]) reviews the database to ensure accurate data collection and correct data export for future analyses. The data is read into SAS from REDCap and descriptive statistics are generated to check for missing data and to check for out-of range values. The research staff maintains a log of all data entry procedures which includes data collection, and regularly checks the data log to ensure proper data entry procedures. Extensive procedures are in place to minimize missing data, including a database that automatically flags any missing data when subjects are completing questionnaires, double-checks any data points and thoroughly checks every form before participants leave their evaluation visits and interventions.

### Data and safety monitoring

We have established an National Institutes of Health-approved independent DSMB. The DSMB team is comprised of investigators with expertise in rheumatology clinical trials, statistical design, exercise, and adverse events. Members of the DSMB do not have any affiliation with Tufts Medical Center. The DSMB is responsible for monitoring the project, subject safety and adequacy of data quality. We provide to the DSMB a number of reports including serious adverse events or death within 24 hours of knowledge of event occurrence, annual reports of all adverse events as well as routine progress reports prior to each DSMB meeting.

### National Institute of Health site visits

The National Center for Complementary and Integrative Health (NCCIH)/National Institute of Health initiated a clinical site monitoring program for the trial. The site monitoring has assisted both NCCIHand its investigators in fulfilling our mutual responsibilities of ensuring participant safety, ensuring adherence of studies to applicable regulations, and verifying data quality, completeness and accuracy. NCCIH expanded this monitoring program across the portfolio, with the goal of implementing routine initial site monitoring for most interventional studies as well as large observational projects. The NCCIH Office of Clinical and Regulatory Affairs established a contract for the NCCIH Clinical Studies Monitoring Service with Westat, a Maryland-based contract research organization. Westat staff conduct pre-enrollment site visits for studies that are beginning enrollment and periodic interim site visits after enrollment is initiated. The initial Westat represented NCCIHsite visit convened on 14 March 2012. The site monitor establishes a guideline for monitoring the study periodically which includes review the protocol, informed consent forms, case report forms, data and safety monitoring plans and data quality.

